### Data and safety monitoring

A data and safety monitoring board (DSMB) has been established for the two AM intervention trials, given that many children enrolled in the novel intervention arms may receive less specially-formulated foods in their treatment than in the standard of care models. The DSMB will periodically review and evaluate the accumulated study data for participant safety, study conduct, and progress. Significant adverse events will be reported to the DSMB on an ongoing basis as they occur.

Masked outcome data will be provided to the DSMB after approximately every 600 subjects in each treatment trial have completed their treatment and been classified as either recovered or not. Given the goal of enrolling 2400 children in each trial, this equates to three interim analyses (at 600, 1200, and 1800 outcomes per trial). The O’Brien-Fleming boundary [42] will be used by the DSMB to recommend stopping early any experimental arm in case that arm’s recovery rate or mortality rate is significantly worse than the control arm.

DSMB recommendations to stop an experimental arm will be taken up by the MODAM study principal investigators and external technical advisory group for consideration as soon as possible after the recommendation is made. Any children currently enrolled in the trial if and when a decision is made to close an experimental arm will be transferred to standard of care (control arm) and will have their data censored as a non-study enrollment.

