**Final Outcome = Recovered**			
	Recovered	Recovered	Anthropometry has reached recovery criteria for 2 consecutive visits within 16 weeks of enrollment

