**Final Outcome = Not Recovered**			
	−	Deteriorated to SAM	Anthropometry worsened from MAM to SAM since previous visit
	Died	Died	Death since previous visit
	Hospitalization	Hospitalization	Child hospitalized for medical or nutritional deterioration
	Lost to follow-up	Lost to follow-up	Child unable to be located for three consecutive visits
	Remained with AM	Remained with AM	Child has not achieved recovery criteria after 16 weeks of therapy

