The α parameter (Type I error) will be set at 0.05, indicating a 5% risk of identifying a difference between an experimental group and the control group where none really exists. The β value (Type II error) will be set at 0.20, thereby giving a power of 80% to identify a difference between an experimental group and the control arm. Due to possible incorrect enrollments, incomplete or inaccurate data collection, and/or drop-outs, we will aim to enroll an additional 10% in each study arm beyond the sample size target calculation.

Based on these parameters, we determined that the minimum sample size needed for a non-inferiority margin of 6% is 798 children per study arm; the minimum needed for a non-inferiority margin of 8% is 462 children per study arm; for 10%, the minimum needed for 10% would be 305 [28]. Multiplying the largest of these by three study arms per trial gives a targeted sample size for enrollment of 2400 children in each trial. This warrants an enrollment of an average of 140 children per month in each trial. If enrollment is slower than anticipated, requiring an adaptation to the enrollment goal, then 1400 children in each trial will be sought to achieve a non-inferiority margin of 8% in a three-armed trial, or 915 for a 10% non-inferiority margin.

### Post-recovery– trial 3

Children from all 3 arms in each of the 2 AM intervention trials who achieve anthropometric recovery within 16 weeks of enrollment will then be offered enrollment into the third of the three integrated trials encompassed by the MODAM study (Fig. 1). This post-recovery trial aims to offer insights into numerous outstanding questions in the AM field, given that high rates of post-recovery relapse and mortality place heavy burdens on operational SAM and MAM treatment programs [16, 29]. High post-SAM relapse is a notable problem in Ethiopia, where such cases make up a high proportion of CMAM enrollments [30–32].

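### DSMB looks counted in already-classified children do not estimate 16-week recovery, because one failure class exists only after week 16; the bias can go either way and its effect on stopping is modest

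*Protocol article*

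**What the plan says.** Under *Data and safety monitoring*, masked outcome data go to the DSMB "after approximately every 600 subjects in each treatment trial have completed their treatment and been classified as either recovered or not". The section describes these as "three interim analyses (at 600, 1200, and 1800 outcomes per trial". The stopping rule is of O'Brien-Fleming type: that "boundary [42] will be used by the DSMB to recommend stopping early any experimental arm" whose recovery or mortality rate is significantly worse than control.

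The powered endpoint, under *Intervention trials 1 and 2 sample size*, is recovery by 16 weeks. Table 2 sets when each class can be recorded:
- Recovered: "Anthropometry has reached recovery criteria for 2 consecutive visits within 16 weeks of enrollment". With weekly SAM visits and fortnightly MAM visits, this can be recorded from about week 2 or week 4.
- Deteriorated to SAM (MAM trial only): "Anthropometry worsened from MAM to SAM since previous visit", so at any follow-up visit.
- Lost to follow-up: "Child unable to be located for three consecutive visits", so from about week 3 (SAM) or week 6 (MAM).
- Died, Hospitalization: when they occur.
- Remained with AM: "Child has not achieved recovery criteria after 16 weeks of therapy".

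On accrual, the sample size section says: "This warrants an enrollment of an average of 140 children per month in each trial".

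**The concern.** A look triggered by a count of classified children mixes two groups. Children enrolled more than 16 weeks ago all have an outcome. Children enrolled more recently contribute only if something has already happened to them, and that cannot be *Remained with AM*. The recovered share among those classified then depends on how quickly recoveries and failures are recorded, as well as on how many children recover by week 16.

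If arms differ in those timings, the boundary is applied to a difference that is partly an artefact. A harmful arm could look better than it is, or a slower arm with equal 16-week recovery could look worse. The consequence is real: when an arm closes, children then on it move to control and their data are censored as non-study enrolments. Death rates taken over classified children share the same denominator problem.

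**Working it through.** **Inputs from the protocol.** 2400 children per trial; looks at 600, 1200 and 1800 outcomes; 140 enrolled per month; 75% anticipated recovery; 16 weeks' maximum treatment.

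**The plan's own figure.** 2400/600 − 1 = 3 interim looks, as stated, with about 200, 400 and 600 children per arm. The article gives no other operating figure for the looks.

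**Children in the window.** 140 × 12/52 = 32.3 per week; 32.3 × 16 ≈ 517, nearly as many as one look.

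**Bias in the pooled rate.** Let *a* be weekly accrual, *p* true 16-week recovery, and *m_r*, *m_f* the mean weeks to classification of recoveries and failures. Under steady accrual, once week 16 has passed, classified children at time T number a(T − m), where m = p·m_r + (1 − p)·m_f. Recovered children number a·p(T − m_r). At N classified:

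observed rate = p + p(1 − p)(m_f − m_r)·a/N

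With p = 0.75, each week by which failures are recorded later than recoveries adds 0.1875 × 32.3/600 = 1.0 point at look 1, 0.5 at look 2 and 0.3 at look 3. The sign follows m_f − m_r.

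The article gives neither recovery times nor a failure mix, so both are assumed. With m_r = 8 weeks:

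| Failures recorded | m_f | 600 | 1200 | 1800 |
|---|---|---|---|---|
| All at week 16 | 16 | 83.1% | 79.0% | 77.7% |
| A quarter at week 6, rest at 16 | 13.5 | 80.6% | 77.8% | 76.9% |
| Three quarters at week 6, rest at 16 | 8.5 | 75.5% | 75.3% | 75.2% |
| All at week 4 | 4 | 71.0% | 73.0% | 73.7% |

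First row, look 1: 0.75 + 0.1875 × 8 × 32.3/600 = 0.831. Varying the mean recovery time as well, look 1 ranges from 66.9% to 87.1%.

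**Arm differences and crossing.** These come from simulation: 1500 trials per scenario, a quarter of failures at week 6, and O'Brien-Fleming z = 4.05, 2.86, 2.34. The article gives no alpha for the boundary; four stages at one-sided 0.025 are assumed. The comparator is the first 600, 1200 and 1800 enrolled, followed to week 16. Differences are experimental minus control, in points.

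| True recovery, control/exp. | Mean weeks to recovery, control/exp. | Difference seen at 600 / 1200 / 1800 | Any interim crossing: classified vs complete cohort |
|---|---|---|---|
| 75/75 | 8/8 | about 0 at each look | 1.1% vs 1.2% |
| 75/75 | 8/10 | −1.6 / −0.9 / −0.6 | 1.8% vs 0.9% |
| 75/75 | 6/10 | −3.2 / −1.9 / −1.3 | 4.5% vs 1.5% |
| 75/75 | 10/8 | +1.6 / +0.8 / +0.5 | 1.0% vs 1.6% |
| 75/65 | 8/8 | −8.8 / −9.4 / −9.7 | 91.9% vs 92.7% |
| 75/65 | 8/7 | −7.8 / −8.9 / −9.3 | 89.4% vs 92.8% |

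The simulation error of a 1.8% figure is √(0.018 × 0.982/1500) ≈ 0.3 points, so only the 4-week gap gives a clearly raised false-crossing rate.

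**A true 10-point deficit can shrink or grow.** Take 15% *Remained with AM* and 10% early exits in control, recovery at a mean of 8 weeks. If the extra failures are all *Remained with AM*, the deficit appears as about 7.5 points at look 1. If they are all early, it appears as 11.5.

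**Against the boundary.** At look 1, 4.05 × √(2 × 0.75 × 0.25/200) ≈ 0.175, so a gap of about 17 points is needed. At look 3, 2.34 × √(2 × 0.75 × 0.25/600) ≈ 0.058, about 6 points. The bias is largest where the boundary is strictest.

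**The case against.** The strongest reply is that the section fixes when data go to the DSMB, not the analysis set or estimator. It also says the board reviews accumulated study data, and *Statistical analyses* names Kaplan-Meier for recovery rates. A DSMB charter, not shown, may define a proper cut. This stands in part: use of classified children only is the natural reading of looks defined as outcomes, but it is not stated outright. Kaplan-Meier is not tied to the looks, and the trigger itself is fixed in the text, so more than omitted detail is at issue.

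A reader might infer that interim recovery is overstated and arm differences distorted as a matter of course. The documents do not support that. All but one failure class can be recorded before week 16: three of four in the SAM trial, four of five in the MAM trial. On fortnightly visits with 20% early failures and 5% *Remained with AM*, the observed rate is 74.9%, 75.0% and 75.0%. With equal rates and timing there is no arm bias.

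Nor does the protocol expect every dose to change recovery speed. It anticipates faster recovery for MAM experimental group B only; no section anticipates a slower experimental arm with equal 16-week recovery, which is the false-stop case.

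Two further points stand. The 140 per month is the rate the target requires, and the protocol warns of slower enrolment; the bias is proportional to accrual, so half the rate halves it. For mortality, significant adverse events reach the DSMB as they occur, which limits that part of the concern.

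**Conclusion.** The concern holds in a limited form. If the boundary is applied to the classified children, the interim statistic is not the trial's endpoint, and neither the size nor the sign of its bias can be known beforehand. Overstatement is likely if *Remained with AM* dominates the failures: roughly 2 to 8 points at look 1 with mean recovery at 8 weeks, less later. The *Discussion* makes late failure plausible, since it expects the all-criteria recovery definition to risk longer stays and more failures. Mostly early failures would remove or reverse the bias.

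Arm distortion needs arms that differ in recovery speed, failure timing or recovery rate. It is then about 1 to 3 points at look 1 and about 1 point at look 3. For MAM group B, the anticipated faster recovery would flatter that arm. Detection of a true 10-point deficit falls by about 1 to 3 percentage points in the two cases simulated. The final analysis is untouched unless an arm is stopped. Severity is low to moderate and confidence moderate, since timings, failure mix and boundary alpha are all assumed.

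**What to change.** State the interim analysis set. At each look, restrict the recovery comparison to children randomised at least 16 weeks, plus a short visit window, before the data cut. Either trigger the looks when 600, 1200 and 1800 children have reached that point, or keep the calendar timing and use the smaller complete cohort. Alternatively, specify a time-to-event estimate of 16-week recovery that includes children still on treatment and keeps deaths, hospitalizations, losses and deteriorations as non-recoveries. Report deaths over all randomised children or child-time.

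The cost is a change to the data-cut wording plus some delay or loss of numbers. Assume recovery at a mean of 8 weeks, 15% *Remained with AM* at week 16 and 10% early exits at a mean of 5.5 weeks. Mean classification time is then 0.75 × 8 + 0.15 × 16 + 0.10 × 5.5 = 8.95 weeks. Waiting for 600 complete children delays the first look by 16 − 8.95 ≈ 7 weeks. Keeping the date leaves (600/32.3 + 8.95 − 16) × 32.3 ≈ 370 children. The time-to-event option avoids both, at the price of a more complex interim statistic.

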### Intervention trials 1 and 2 follow-up visits during treatment

Children will be reassessed at health posts and health centers during follow-up visits every 7 days (SAM trial) or every 14 days (MAM trial) for up to 16 weeks after the time of enrollment, the maximum length of stay prescribed in the Ethiopian national guidelines. At each follow-up visit, a full set of anthropometric measurements will be reassessed, recent infectious symptoms (vomiting, diarrhea, fever, cough) will be queried of the caregiver, and appropriate appetite verified.

Children who appear to be progressing towards recovery will receive additional allotments of their assigned intervention. Children who are not progressing well (e.g., poor weight gain, feeding or health concerns expressed by their caregivers, poor clinical appearance including medical complications, etc.) will be either re-engaged in nutritional and health counseling, including the importance of full adherence to the allocated intervention, or referred to a higher level of care. Clinical assessments for complications will be completed similar to enrollment.

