### Intervention trials 1 and 2 sample size

The powered objective for the AM intervention trials will be the rates of anthropometric recovery by 16 weeks (Table 2), comparing each intervention group individually against the standard of care (control) group, based on the hypothesis that the novel interventions are non-inferior.

A 2020 systematic review of treatment outcomes among children treated for SAM as outpatients with the standard dosing of RUTF showed an average recovery rate of 70% [24]. In Ethiopia specifically, a recent study in Gondar found approximately 75% of children with SAM treated as outpatients recovered [25]. Another recent study in Oromia found that children enrolled by MUAC alone had a recovery rate of approximately 85% [26]. Less complete outcome data exists for children with MAM, but an operational study from southern Ethiopia demonstrated a 73% recovery rate for children with MAM treated with RUSF [27]. Based on these accumulated data, we have powered the study based on an anticipated recovery rate of 75% for both the SAM and MAM studies.

The non-inferiority margin that is considered clinically acceptable is a relatively subjective judgment that needs to incorporate local sociocultural preferences and economic considerations. Trial cost and duration limitations must also be considered. To help inform this decision, we conducted interviews with health care workers and community leaders within Ethiopia, as well as discussions with our technical advisory groups. There was consensus that a non-inferiority margin of 5–10% would be considered clinically useful, although there was a notable preference for as small of a margin as would be feasible to provide the most robust data, especially compared to prior trials of modified dosing regimens which have used comparatively larger non-inferiority margins. Given resource constraints, we will thus aim for a non-inferiority margin of 6% for each trial, but may have to compromise to up to 10% if enrollment challenges arise.

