### Statistical analyses

Standard statistical approaches will be used in each of the three trials to analyze each intervention arm independently in comparison to the control arm. Dichotomous variables will be compared using Chi-square testing. Continuous variables will be analyzed using the Student t-test. Rates of recovery and relapse will be evaluated using Kaplan-Meier survival analyses. Regression analyses will be used as appropriate to control for confounding variables. In general, P values less than 0.05 will be considered statistically significant, although this will be reduced in the case of multiple comparisons. 95% confidence intervals will be calculated in addition to P values in order to provide additional detail about error margins in the various calculations. Intention-to-treat analyses will be used throughout, as this will provide the most pragmatic and applicable evidence to inform the real-world scale-up of these interventions.

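### Children still in treatment when an experimental arm closes are reclassified as outside the study, which contradicts intention-to-treat and can understate that arm's recovery deficit

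*Protocol article*

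**What the plan says.** Data and safety monitoring: the DSMB receives outcome data "after approximately every 600 subjects in each treatment trial have completed their treatment and been classified as either recovered or not", that is at 600, 1200 and 1800 outcomes per trial. It may recommend closing an experimental arm whose recovery or mortality crosses an O'Brien-Fleming boundary. Children enrolled at closure "will be transferred to standard of care (control arm) and will have their data censored as a non-study enrollment".

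Statistical analyses: "Intention-to-treat analyses will be used throughout, as this will provide the most pragmatic and applicable evidence". No exception is made for a closed arm. The same section adds: "Rates of recovery and relapse will be evaluated using Kaplan-Meier survival analyses".

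The powered endpoint is "rates of anthropometric recovery by 16 weeks (Table 2), comparing each intervention group individually against the standard of care (control) group". Treatment visits run "for up to 16 weeks after the time of enrollment, the maximum length of stay prescribed in the Ethiopian national guidelines". In Table 2, the category for children who remain malnourished is defined as "Child has not achieved recovery criteria after 16 weeks of therapy". Death, hospitalization, loss to follow-up and (MAM trial) deterioration can be classified earlier.

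**The concern.** These children were eligible, consented, randomised and treated. Declaring them non-study afterwards is a post-randomisation exclusion, which the intention-to-treat statement rules out.

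The exclusion also depends on outcome. A child who recovers leaves treatment at once and is counted as a success. A child who will not recover mostly waits until week 16 to be counted. The children in treatment on any given day therefore contain too many slow recoverers and eventual non-recoverers, along with recent enrolees. Removing them raises the closed arm's apparent recovery rate.

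A closed arm is where the trial most needs an unbiased estimate, because the result would inform dosing policy. If its deficit is understated, an arm stopped for poor recovery may be reported with a deficit smaller than the margin.

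**Working it through.** **Figures in the article.** It gives no figure for the effect of this rule. Its 798 per arm reproduces with 75% v 69%, one-sided alpha 0.05, 80% power, a continuity correction and 10% inflation. The sidedness of the stopping boundary is not stated, so both versions were run: 4.05/2.86/2.34 at the three looks (two-sided 0.05) and 3.47/2.45/2.00 (one-sided 0.05).

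**Inputs.** From the article: 140 children a month per trial, three arms, control recovery 75%, 16-week limit, looks at 600/1200/1800 outcomes. Assumed: mean recovery time 6-10 weeks, 10-40% of failures before week 16, true experimental recovery 55-69%, no delay between data cut and closure, and no change in outcome after transfer.

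**Step 1: how many are dropped.** Weekly accrual per arm = 140 × 12 / 52 / 3 = 10.8. Number in treatment = weekly accrual × mean stay. Take true recovery 65%, mean 8 weeks to recovery, 10% of failures early (placed at 8 weeks on average):
- mean stay = 0.65 × 8 + 0.35 × (0.9 × 16 + 0.1 × 8) = 5.20 + 5.32 = 10.5 weeks
- in treatment = 10.8 × 10.5 ≈ 113
- eventual non-recoverers among them = 5.32 / 10.52 = 51%, against 35% of all children randomised

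Simulation (1,200 trials per scenario, 800 per arm) gives 100-120 dropped: 33-37% of the arm's enrolment at look 1, 20-22% at look 2, 14-16% at look 3. Non-recovery is 48-67% among the dropped and 28-41% among the kept.

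**Step 2: effect on the closed arm's rate.** Non-recovery among the kept = (N·q − D·f) / (N − D), where N is enrolled, q true non-recovery, D dropped and f non-recovery among the dropped. At look 1, with N = 298, D = 104, q = 0.35, f = 0.50: (104.3 − 52.0) / 194 = 0.27. A true 65% is shown as 73%. Simulation gives about 73%, 69% and 68% at the three looks.

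**Step 3: deficit against control, given that the boundary was crossed.** Selected results, one-sided boundary, in percentage points. The weeks are mean time to recovery (control/experimental where they differ). The percentage is the share of failures before week 16.

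| True rates; timing | Look | Full | Closed arm cut, control completed | Hidden | Trials reporting <6 | Both arms cut | Administratively censored |
|---|---|---|---|---|---|---|---|
| 75 v 65; 8 wk, 10% | 1 | 15.0 | 6.9 | 54% | 33% | 15.4 | 16.6 |
| same | 2 | 11.1 | 6.4 | 42% | 47% | 10.4 | 11.2 |
| same | 3 | 8.4 | 4.9 | 41% | 79% | 7.4 | 8.2 |
| 75 v 65; 8 wk, 40% | 2 | 10.9 | 7.8 | 29% | 20% | 10.6 | 11.1 |
| 75 v 65; 6 wk, 10% | 1 | 15.4 | 5.8 | 62% | 54% | 15.8 | 16.6 |
| 75 v 55; 6 wk, 10% | 1 | 21.8 | 9.9 | 55% | 10% | 18.7 | 22.1 |
| 75 v 55; 8/10 wk, 40% | 2 | 17.5 | 14.0 | 20% | 0% | 16.4 | 17.2 |

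Across all scenarios the average share hidden is 20-62% with the one-sided boundary and 18-51% with the two-sided one. It exceeds half on average only at look 1 with 90% of failures at week 16; at looks 2 and 3 it is 18-49%. With the two-sided boundary, 75% v 65% closed at look 2, a full deficit of 11.7-11.8 becomes 6.4-8.6 and falls below 6 in 8-44% of such closures. A second simulation, with a median of about 7 weeks to recovery, gives 15-36% hidden.

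**The case against.** **The word censored may be meant in its survival-analysis sense.** The article names Kaplan-Meier for recovery, and under administrative censoring there is almost no bias (last column). This reading is possible. But calling the children a non-study enrollment points to removal, and a proportion recovered by 16 weeks compared by chi-square cannot use a censored child.

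**Control may be cut at the same date.** The article does not say. If it is, most of the bias goes; the largest loss in the table is 21.8 to 18.7. The mixed comparison is therefore an assumption, though nothing in the article excludes it. The rule's opening words could be read as covering children in all three arms, but a control child cannot be transferred to control, so the closed arm alone is probably meant.

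**A reader might infer that most of the harm is hidden**, by setting 73% at look 1 against a control rate of 75%. That does not follow. With about 200 completers per arm, a true 10-point deficit appears as 7.4 among completers (about 80.5% v 73.1%). Then z = 7.4 / 4.2 ≈ 1.8, against a boundary of 4.05 or 3.47. Such an arm closes on recovery in about 1% or 4% of trials, and those trials have larger observed deficits. Deaths before closure are final outcomes in Table 2 and stay counted.

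**A reader might also want the DSMB looks changed**, since completers flatter both arms. Reviewing completed outcomes is an ordinary design and the effect on decisions is small: at look 1 a true 75% v 69% appears as 80.7% v 76.0%, moving z from 6.0 / 4.5 ≈ 1.3 to 4.7 / 4.1 ≈ 1.1, far below either boundary.

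**Conclusion.** The point holds. The closure rule contradicts the intention-to-treat statement and, read as removal, drops about 100-120 children of the closed arm selectively. If controls are followed to completion, roughly 15-50% of the recovery deficit is hidden given a boundary crossing, with more than half only in some first-look closures. These sizes rest on assumed recovery timing and on the mixed comparison.

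The reported deficit can fall inside the 6-point margin, but that concerns the point estimate. A reader might infer that a stopped arm could be declared non-inferior; the figures do not support this. At look 2, with about 397 kept and 507 controls, the standard error is √(0.31 × 0.69 / 397 + 0.25 × 0.75 / 507) ≈ 3.0 points, so a reported deficit of 6.4 has an upper one-sided 95% bound of about 6.4 + 1.645 × 3.0 = 11.3.

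The rule matters only if an arm is closed. The wording should be settled before that happens, because one reading is nearly unbiased and the other is not.

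**What to change.** Separate the analysis from the care decision, which this point leaves untouched.

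1. Delete the words that make these children a non-study enrollment.
2. State that every child randomised before closure is analysed in the assigned arm and compared with concurrently randomised controls.
3. Name one primary estimate of 16-week recovery for a closed arm: either all these children followed to 16 weeks (intention-to-treat), or cumulative incidence of recovery with administrative censoring at the closure date in both arms.
4. Add a sensitivity analysis in children enrolled at least 16 weeks before closure, who are selected by enrolment date and not by outcome.
5. State that data from the control arm and the continuing experimental arm are unaffected.

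The cost is protocol wording and slightly more analysis work. Under the first option, recent enrolees contribute diluted information because their care changed at closure. Under the second, some contribute only censored time.
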